### Unpowered Secondary Endpoints

• The mean Oswestry Disability Index score, as well as the mean improvement, will be compared between groups across all study visits. The incidence of both 15% and 15 point improvements will also be compared.

• Quality of Life, measured using the Short Form-36 Questionnaire (SF-36); improvement of 15% in the overall score at 24 months compared to baseline will be considered clinically significant.

• Disc height (incidence of 3 mm change), as measured by standard lateral radiograph. Comparison of disc height to the 6-week height will also be performed to account for the expected degree of immediate post-operative "settling" of the prosthesis.

• Incidence of subsidence of the device (> 3 mm) at the 24-month visit.

• Neurological status at 24 months compared to baseline.

• The mean operative time.

• Safety: The individual incidence rates of all adverse events through 24 months follow-up.

• Each subject will remain in the study for 5 years post treatment. It is expected to take 6 years to collect all required data for this study.

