**RADIOGRAPHIC EVENTS**									
MRI scan	**X**								
DXA Scan	**X (IR)**								
X-rays, A/P -- Standing Neutral	**X**	**X** **(Implant Position)**	**X** **(Implant Position)**	**X**	**X**	**X**	**X**	**X**	**X**
X-rays, A/P- Right/Left Bending	**X**			**X**	**X**	**X**	**X**	**X**	**X**
X-rays, Lateral - Flexion-Extension	**X**			**X**	**X**	**X**	**X**	**X**	**X**
X-Rays, Lateral Standing Neutral	**X**	**X** **(Implant Position)**	**X** **(Implant Position)**	**X**	**X**	**X**	**X**	**X**	**X**

IR: If required

** Prophylactic antibiotics

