### Power Analysis

Power analysis was performed using the PASS 2005 software. (NCSS Kaysville, Utah)The PASS 2005 output solves for what the true success rate must be in the Activ-L group in order to have 80% power to detect superiority relative to a number of possible success rates in the control group (plausible range 50-80%). All calculations assume a power of 80% and a two-sided significance level of 0.05. Note that for each case, the required margin of improvement is not particularly onerous. For example, if the true success rate in the control group is 50%, the true success rate in the treatment group need only be 68%. If the control rate is 80%, the Activ-L rate need only be 92%.

Therefore, with the sample size required to demonstrate the primary composite endpoint, this study is adequately powered to detect a reasonable, yet clinically meaningful difference in rates if Activ-L truly produces greater improvement in pain over time. Please refer to table 2.

**Table 2 T2:** Power Analysis results using PASS 2005 Software (NCSS Kayesville, Utah) PASS 2005 Power Analysis Results.

	Sample Size Group 1	Sample Size Group 2	Group 1 or Treatment	Group 2 or Control	Diff if H0	Diff if H1		
Power	N1	N2	P1.1	P2	D0	D1	Target Alpha	Beta
0.8000	178	89	0.6771	0.5000	0.0000	0.1771	0.0500	0.2000
0.8000	178	89	0.7227	0.5500	0.0000	0.1727	0.0500	0.2000
0.8000	178	89	0.7665	0.6000	0.0000	0.1665	0.0500	0.2000
0.8000	178	89	0.8086	0.6500	0.0000	0.1586	0.0500	0.2000
0.8000	178	89	0.8487	0.7000	0.0000	0.1487	0.0500	0.2000
0.8000	178	89	0.8865	0.7500	0.0000	0.1365	0.0500	0.2000
0.8000	178	89	0.9218	0.8000	0.0000	0.1218	0.0500	0.2000

Two Independent Proportions (Null Case) Power Analysis Numeric Results of Tests Based on the Difference: P1 - P2 H0: P1-P2 = 0. H1: P1-P2 = D1 <> 0. Test Statistic: Z test with pooled variance

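### The only metric the protocol names for disc height is the incidence of a 3 mm change; under a normal model this discards at least about a third of the information in a millimetre measurement

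*Protocol article*

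**What the plan says.** The section Unpowered Secondary Endpoints of the protocol article has a disc-height bullet with two parts. The first names the metric: "Disc height (incidence of 3 mm change), as measured by standard lateral radiograph". The second adds another reference time: "Comparison of disc height to the 6-week height will also be performed to account for the expected degree of immediate post-operative" settling of the prosthesis. The second part gives the reference film but no scale. It promises neither a comparison of mean millimetres nor a comparison confined to the 3 mm cut. The bullet does not say whether a change is a loss, a gain or either.

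Two neighbouring bullets matter. For the disability score the plan fixes both kinds of analysis: "The mean Oswestry Disability Index score, as well as the mean improvement, will be compared between groups across all study visits", followed by responder cuts. For the device itself there is a separate threshold count: "Incidence of subsidence of the device (> 3 mm) at the 24-month visit".

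Table 1 schedules "X-Rays, Lateral Standing Neutral" at baseline and at every follow-up visit. It also schedules these films during surgery and at discharge, but labels those two as being for implant position. The exclusion criteria use a pre-operative disc-height limit, so pre-operative height is assessed in each candidate. The article gives no SD, expected change, event rate or hypothesis for disc height.

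**The concern.** A 3 mm count treats a subject with a 2.9 mm change like one with no change, and a subject at 3.1 mm like one at 6 mm. A device difference that lies mostly below 3 mm therefore shows up only through the few subjects whom it moves across the line. Such a difference is plausible here. The Background contrasts single-unit insertion of Activ-L with the controls' second distraction step, and the disc-height bullet itself expects some settling.

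At stake is the precision of a descriptive device comparison. If the 3 mm rates look similar, a reader may take disc height to be equally maintained, although the named metric had little chance of showing otherwise. The disability-score bullet shows that the authors were ready to report a mean beside a responder rate, and disc height could be handled in the same way.

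**Working it through.** **Inputs from the protocol.** Group sizes are 178 Activ-L and 89 control (Table 2). The test is a pooled-variance Z test for two proportions. On error rates: "All calculations assume a power of 80% and a two-sided significance level of 0.05". Table 2 does not concern disc height; I borrow only its sample size and test.

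**Inputs that I assume, because the documents give none.** Disc-height change is normal, with the same SD in both groups. A 3 mm change is counted in one direction. The control rate of a 3 mm change runs from 2% to 50%. The true difference between groups is 0.2, 0.3 or 0.4 SD.

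**Step 1: reproduce the plan's own figure.** In the text, "if the true success rate in the control group is 50%, the true success rate in the treatment group need only be 68" percent; Table 2 gives 0.6771.
- Power = Φ[(d − 1.96 × SE0)/SE1], with SE0 from the pooled rate and SE1 from the separate rates.
- Pooled rate = (178 × 0.6771 + 89 × 0.5)/267 = 0.6181.
- SE0 = √[0.6181 × 0.3819 × (1/178 + 1/89)] = 0.0631.
- SE1 = √[0.6771 × 0.3229/178 + 0.25/89] = 0.0635.
- Power = Φ[(0.1771 − 1.96 × 0.0631)/0.0635] = 0.800, as stated.

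The other six rows also reproduce (0.7997 to 0.8002), so the formula is the one the plan used.

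**Step 2: information kept by a cut.** For a normal variable cut at the point c that gives event rate p, the efficiency relative to a comparison of means, for a small shift, is φ(c)²/[p(1 − p)].

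| Rate of 3 mm change | 2% | 5% | 10% | 20% | 30% | 50% |
|---|---|---|---|---|---|---|
| Relative efficiency | 0.12 | 0.22 | 0.34 | 0.49 | 0.58 | 0.64 |

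The maximum, 0.64, is at 50%. The loss is therefore at least 1 − 0.64 = 36% at any rate, and it passes one half below about 20%. The formula is symmetric in p and 1 − p, so rates above about 80% lose as much.

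**Step 3: power at 178 and 89.** For means, power = Φ[δ/√(1/178 + 1/89) − 1.96], and the root is 0.1298. At δ = 0.3 SD this is Φ(2.31 − 1.96) = 0.64. For the incidence, the control rate fixes c and the Activ-L rate follows from the shift. At a 5% control rate, c = 1.645 and the Activ-L rate is 1 − Φ(1.345) = 8.9%. The formula of Step 1 then gives 0.19.

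| Shift | Means | Incidence at control rate 5% | 10% | 20% | 30% | 50% |
|---|---|---|---|---|---|---|
| 0.2 SD | 34% | 10% | 14% | 18% | 21% | 23% |
| 0.3 SD | 64% | 19% | 27% | 37% | 42% | 45% |
| 0.4 SD | 87% | 32% | 46% | 60% | 66% | 69% |

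These rows take Activ-L to have more 3 mm changes. With the shift the other way, at 0.3 SD, the incidence has 20% to 41% at control rates of 5% to 30%.

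**Step 4: the same in millimetres.** Take an assumed mean loss of 0.5 to 2 mm, an assumed SD of 1 to 2 mm, and a shift that favours Activ-L. The shift that gives 80% power for means is (1.96 + 0.84) × 0.1298 = 0.364 SD. Tested as the incidence of a 3 mm loss, that shift has 11% to 55% power.

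**The case against.** The strongest reply has four parts.

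**The bullet is open on scale.** A reader might infer that disc height is compared only as a 3 mm incidence. The documents do not support that. The 6-week comparison speaks of disc height and is not tied to the cut, so it may well be done in millimetres. What stands is narrower: the incidence is the only metric named, and the text commits to no comparison in millimetres.

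**The size of the loss is not in the documents.** A reader might infer that most of the endpoint's ability to show a difference is gone. That is so only if 3 mm changes are uncommon. At a control rate of 30% and a shift of 0.4 SD, the incidence keeps 66% power against 87%. With no rate or SD given, only the floor of about a third can be stated, and that also needs the normal model.

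**The details may be in an analysis plan that is not shown.** An article can leave tabulation of means to that plan, and the quality-of-life bullet in the same list also gives only a threshold. This lowers the weight of the point. It does not remove it, because the article does more than stay silent: it names a metric, and that metric is a dichotomised one.

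**The endpoint carries little.** It is listed under "Unpowered Secondary Endpoints", is outside the primary composite and has no hypothesis. A count of subjects past a threshold is a legitimate radiographic summary and should stay.

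One further inference should be resisted, namely that the subsidence endpoint makes the disc-height count redundant. Disc-height change has no stated direction, while subsidence is a movement of the device. Nothing shows that the two count the same subjects.

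**Conclusion.** The point holds as a minor one. The only metric named for disc height is the incidence of a 3 mm change. Under normal change with equal SDs and a one-directional cut, this discards at least 36% of the information on a between-group difference, and more than half if fewer than about 20% of subjects have such a change. At an assumed 0.3 SD shift and Table 2's group sizes, power is 64% for means against 19% to 42% for control rates of 5% to 30%.

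The rates and shifts are assumptions, so these figures illustrate the cost and do not predict this trial's power. The documents speak of change, so reading the endpoint as height loss goes beyond them. No primary or powered conclusion is affected.

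**What to change.** State in the disc-height bullet, or in the analysis plan, that:

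1. Disc height in mm at 24 months is compared between groups as a difference in means with a 95% CI, from a linear model adjusted for pre-operative disc height (baseline lateral film) and site.
2. Mean change in mm from the 6-week film is reported as a separate, unadjusted supportive comparison.
3. The incidence of a 3 mm change is kept as a companion rate, with its direction and reference film stated.

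No post-operative height should enter the model as a covariate. It is measured after randomisation and the device can affect it, so adjusting for it could remove the early settling difference that the comparison is meant to show. The discharge film is a doubtful reference in any case, because Table 1 labels it for implant position and does not say that height is read from it.

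The cost is a few lines of wording and one more reported estimate for an exploratory endpoint. The baseline, 6-week and 24-month lateral films are already scheduled, so no new films or subjects are needed.

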### Power Analysis

Power analysis was performed using the PASS 2005 software. (NCSS Kaysville, Utah)The PASS 2005 output solves for what the true success rate must be in the Activ-L group in order to have 80% power to detect superiority relative to a number of possible success rates in the control group (plausible range 50-80%). All calculations assume a power of 80% and a two-sided significance level of 0.05. Note that for each case, the required margin of improvement is not particularly onerous. For example, if the true success rate in the control group is 50%, the true success rate in the treatment group need only be 68%. If the control rate is 80%, the Activ-L rate need only be 92%.

Therefore, with the sample size required to demonstrate the primary composite endpoint, this study is adequately powered to detect a reasonable, yet clinically meaningful difference in rates if Activ-L truly produces greater improvement in pain over time. Please refer to table 2.

**Table 2 T2:** Power Analysis results using PASS 2005 Software (NCSS Kayesville, Utah) PASS 2005 Power Analysis Results.

	Sample Size Group 1	Sample Size Group 2	Group 1 or Treatment	Group 2 or Control	Diff if H0	Diff if H1		
Power	N1	N2	P1.1	P2	D0	D1	Target Alpha	Beta
0.8000	178	89	0.6771	0.5000	0.0000	0.1771	0.0500	0.2000
0.8000	178	89	0.7227	0.5500	0.0000	0.1727	0.0500	0.2000
0.8000	178	89	0.7665	0.6000	0.0000	0.1665	0.0500	0.2000
0.8000	178	89	0.8086	0.6500	0.0000	0.1586	0.0500	0.2000
0.8000	178	89	0.8487	0.7000	0.0000	0.1487	0.0500	0.2000
0.8000	178	89	0.8865	0.7500	0.0000	0.1365	0.0500	0.2000
0.8000	178	89	0.9218	0.8000	0.0000	0.1218	0.0500	0.2000

Two Independent Proportions (Null Case) Power Analysis Numeric Results of Tests Based on the Difference: P1 - P2 H0: P1-P2 = 0. H1: P1-P2 = D1 <> 0. Test Statistic: Z test with pooled variance

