## Methods/Design

The following study was reviewed and approved by the Yale University Human Investigation Committee.

The study proposed is a prospective, randomized, single-masked, controlled, multi-center clinical trial consisting of an estimated 414 subjects with single-level DDD of the lumbar spine (L4/L5, or L5/S1) who have failed to improve with conservative treatment for at least six months prior to enrollment. After enrollment, subjects will be randomized in a 2:1 ratio to either the Activ-L Disc (investigational device) or the control (Charité or ProDisc-L). Each investigational site will have a separate, blocked randomization schedule. Fifteen (15) to 20 investigational sites will participate in the investigation. Sites will be encouraged to randomize a minimum of 10 subjects per site and to implant a minimum of four control devices and sites are bound by a maximum of 64 subjects. The first three subjects at each investigational site will receive the Activ-L Disc and will be not be randomized, these patients will be outside of the trial. The purpose of these procedures will be for Surgeon training. Investigators who have already undergone training in implantation of the control disc will be selected for participation; however, for any participating investigator who has not performed at least three prior control implantations, up to three nonrandomized control implantations may also be performed prior to enrolling randomized subjects into the study. This will ensure that experience and proficiency with the implantation method for both discs is comparable. Thus, the maximum total enrollment in the study, including both randomized and nonrandomized cases, is 414 consisting of 261 Activ-L (216 randomized and 45 nonrandomized) and 153 controls (108 randomized and 45 nonrandomized controls). Please refer to figure 1.

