### Powered Secondary Endpoints

• Back Pain, measured at rest using a visual analog scale (VAS); improvement of 20 mm or more on a 100 mm VAS scale at 24 months compared to baseline will be considered clinically significant.

• Leg Pain, measured at rest using a visual analog scale (VAS). The success rate will be formally tested for superiority in the Activ-L group. A patient will be considered a responder if, at the 24 month visit they achieve at least a 20 mm VAS improvement in the leg with the maximum pain at baseline, with no worsening in the other leg.

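### The powered pain responder rates are sized with a z test without covariates; adjusting for baseline VAS and site is a cheap gain, mainly for leg pain

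*Protocol article*

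**What the plan says.** Powered Secondary Endpoints lists two pain outcomes. For back pain, "improvement of 20 mm or more on a 100 mm VAS scale at 24 months compared to baseline will be considered clinically significant". For leg pain, a responder needs a gain of at least 20 mm in the leg that was worse at baseline and no worsening in the other leg. The section states a formal superiority test of the success rate for leg pain only.

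Power Analysis then asks what Activ-L rate would be detectable at the sample size already set by the primary composite endpoint, and ties the answer to improvement in pain. It states: "All calculations assume a power of 80% and a two-sided significance level of 0.05". The first row of Table 2 reads "0.8000 178 89 0.6771 0.5000", and the footnote gives the method: "Test Statistic: Z test with pooled variance".

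Three other places matter:
- **Table 1 and Follow Up Evaluations:** VAS is taken at baseline and at every follow-up visit, for the back and each leg.
- **Methods/Design:** "subjects will be randomized in a 2:1 ratio to either the Activ-L Disc (investigational device) or the control", with a separate blocked schedule for each site.
- **Justification for Pooling Data across Centers:** if the center term is significant and the interaction is not, center effects enter the final models for at least the primary endpoint. Pain is neither included nor excluded.

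**The concern.** A two-sample z test uses nothing about a subject except arm and response. Two things known before surgery could explain part of the variation in response: the baseline pain score and the site.

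Baseline matters most for leg pain. The inclusion criteria require a back VAS of at least 40 mm but set no floor for leg VAS, and they admit subjects with or without leg pain. A subject whose worse leg scores below 20 mm at baseline cannot improve by 20 mm, so is a certain non-responder in either arm. An unadjusted test counts that predictable non-response as noise. Site is a randomization stratum, and strata are normally carried into the analysis.

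What is at stake is precision on the superiority claim for pain, at no cost in patients.

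**Working it through.** **Inputs.** From Table 2: 178 Activ-L and 89 control subjects, two-sided alpha 0.05, power 80%, control rates 50% to 80%. From the inclusion criteria: back VAS at least 40 mm, no leg minimum. The document gives no VAS standard deviation (SD), baseline distribution or baseline-to-24-month correlation, so anything that depends on these is an assumption.

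**Step 1: reproduce Table 2.** Power = Φ[(p1 − p2 − 1.96 × SE_pooled) / SE_unpooled].
- Control 50%: pooled rate (178 × 0.6771 + 89 × 0.5)/267 = 0.6181. SE_pooled = √[0.6181 × 0.3819 × (1/178 + 1/89)] = 0.0631. SE_unpooled = √[0.6771 × 0.3229/178 + 0.25/89] = 0.0635. Power = Φ[(0.1771 − 0.1236)/0.0635] = 0.800.
- Control 80%: SE_pooled = 0.0420, SE_unpooled = 0.0469. Power = Φ[(0.1218 − 0.0823)/0.0469] = 0.800.

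All seven rows reproduce, with power between 0.7997 and 0.8002.

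**Step 2: what baseline carries for leg pain.** Let q be the share of subjects with a worse-leg baseline below 20 mm (assumed; not in the document). They respond with probability 0 in both arms, so the rate among the rest is p/(1 − q). Splitting only on this fact, the variance of the overall difference is

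(1−q)·a(1−a)/178 + (1−q)·c(1−c)/89 + q(1−q)(a−c)²/267, with a = p1/(1−q) and c = p2/(1−q).

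For the control 50% row and q = 10%: a = 0.7523 and c = 0.5556. The variance is 0.000942 + 0.002497 + 0.000013 = 0.003452, so SE = 0.0588 against 0.0635 unadjusted. Power = Φ(0.1771/0.0588 − 1.96) = about 85%. The same formula gives about 82% at q = 5%, 89% at q = 15% and 92% at q = 20%. At q = 0 it gives 80%.

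**Step 3: full baseline adjustment.** A simulation at 178/89 with assumed VAS distributions and a single-leg 20 mm rule, adjusting for baseline only, raised leg-pain power from about 80% to 84-90%. That agrees with Step 2 at moderate q. Site adjustment was not simulated.

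**Step 4: back pain.** Entry at 40 mm or more means every subject can in principle achieve a 20 mm gain, so the mechanism in Step 2 is absent. The simulation showed little or no gain.

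**Step 5: the continuous alternative, for comparison.** If VAS change is normal with equal SD in both arms, the Table 2 rows imply shifts of z(p1) − z(p2) = 0.460 SD (control 50%) to 0.576 SD (control 80%). A comparison of mean change needs (1.960 + 0.842) × √(1/178 + 1/89) = 0.364 SD. ANCOVA multiplies this by √[(1 + r)/2] when baseline and 24-month SDs are equal: 0.293, 0.315 and 0.335 SD for assumed r = 0.3, 0.5 and 0.7.

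**The case against.** The strongest reply is that the z test stands in a power output, not in an analysis section. The article names no final pain model, covariates for secondary endpoints are commonly left to the statistical analysis plan, and an unadjusted power calculation does not exclude an adjusted analysis. This stands. A reader might infer that the pain endpoints will be analysed with an unadjusted z test; the document does not say so.

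Nor is baseline VAS ignored. Both criteria are changes from baseline, and the leg rule uses baseline to choose the leg. Baseline is missing only as a covariate.

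Step 5 may tempt a reader to conclude that the responder test should give way to ANCOVA, with a detectable effect some 30-50% smaller. The document does not support that:
- The 20 mm cut and the two-leg rule are deliberate clinical definitions. A mean difference is another target, and a single-leg ANCOVA does not test the two-leg rule.
- The size of the gain rests on normality, SDs and a correlation that are not given. If the entry floor for back VAS makes the baseline SD 0.6 of the 24-month SD (assumed), ANCOVA needs 0.347-0.361 SD, hardly better than the 0.364 SD for unadjusted change.

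A reader might also infer that the pain question is bound to go unanswered, since a true 10-point advantage gives the z test only 34-61% power across control rates of 50-80%. But the 10-point effect is not in the document, the plan discloses its detectable differences openly, and even ANCOVA with r = 0.5 reaches only about 62% there at a control rate of 50%. Much of the required margin comes from the sample size, not the test.

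What survives is narrower: the responder endpoint can stay exactly as defined and still be tested more efficiently.

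**Conclusion.** The point holds as an optional improvement. The plan contains no arithmetic error and no contradiction here. The only test named for the powered pain endpoints uses no covariate, while a baseline score and a randomization stratum are both available.

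Adjusting for them leaves the data and the endpoint unchanged. For leg pain the expected benefit is a rise in power from about 80% to 84-90%. This rests on assumed baseline distributions, a single-leg version of the rule and baseline adjustment alone. The share of subjects with a worse-leg baseline below 20 mm drives the size, and the document does not give it. For back pain little or no gain should be expected. The effect of site adjustment has not been quantified.

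**What to change.** 1. Keep both 20 mm responder rates as the tested endpoints. State that each is tested with a standardised risk difference from a model containing treatment, baseline VAS and site. For leg pain, the baseline score is that of the worse leg.
2. Label Table 2 as the unadjusted detectable difference: conservative for leg pain, about right for back pain.
3. Report a baseline-adjusted ANCOVA of 24-month VAS as a supportive analysis, not as a replacement for the responder test.
4. Say whether the formal superiority test applies to leg pain only or to back pain as well, so that the adjusted test is attached to the right endpoints.

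The cost is wording, slightly more analysis work, and a model-standardised rate in place of a raw one; raw rates can be shown beside it. One practical matter needs a line in the plan. With 15 to 20 sites, 89 controls average about 6 (89/15) to 4 (89/20) per site, so a rule for combining small sites should be fixed in advance.
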